#### Sensory and Cognitive Functioning

3.4.2

Residents will complete a purposefully developed questionnaire that will ask about their history of hearing, vision and cognitive management before completing objective screening assessments. Both ears will be examined using a Welch Allyn pocket LED otoscope to detect impacted ear wax; where this is present, the client will be referred to a health professional for ear wax removal. Hearing ability will subsequently be screened using HearX HearCheck pure‐tone air‐conduction audiometric testing using a Samsung Galaxy A04e phone with Sennheiser HD280 Pro headphones. Each ear will be tested at 0.5, 1, 2 and 4 kHz, with hearing loss identified if screening thresholds are greater than 35 dB HL in the better ear. Vision screening will include visual acuity screening using PEEK Acuity [44], Spaeth/Richman contrast sensitivity test (SPARCS) [45], central vision testing using an Amsler grid and visual field‐testing using confrontation testing. PEEK acuity will be conducted using a Samsung phone with a screen measuring 13.5 cm by 6.5 cm. PEEK acuity scores are provided in standard units of Snellen—including metric (6/6) and imperial (20/20). SPARCS contrast sensitivity will be conducted using a portable external monitor measuring 17.3 inches. SPARCS evaluates contrast sensitivity across five areas of the visual field: the left upper quadrant, left lower quadrant, right upper quadrant, right lower quadrant and central area. Log‐based scores for each of the five testing regions are scaled from 0 to 20, with the highest possible SPARCS score being 100.

Global cognitive functioning will be evaluated using the hearing or vision impairment version of the Montreal Cognitive Assessment (MoCA) [46, 47]. In the hearing impairment version, three auditory items were substituted with written items [47]; and in the vision impairment version, four visual items were substituted with spoken items. A cut‐off of 24/30 is indicative of cognitive impairment for both versions [46, 47]. Participants with dual sensory impairment will complete the version developed for people with vision impairment with the aid of a personal amplifier, if not wearing hearing aids.

Sensory and cognitive functioning assessment will be conducted by three research assistants with a background in health research and having been trained in hearing and vision assessments by qualified audiologists and optometrists. Additionally, the research assistants will be certified to administer and score the MoCA.

### Outcome Measures

3.5

To evaluate intervention effectiveness, participants will undergo assessment at baseline, throughout the intervention, and at 3 and 6 months post‐intervention. Data will be derived from a variety of methods, including self‐ or proxy‐report questionnaires; long‐term care records; participant observation and qualitative interviews.

#### Primary Outcome

3.5.1

Residents' quality of life will be measured using the interviewer‐administered versions of the HUI‐3 40Q [38] questionnaire with 1‐week recall, and the Quality of Life‐Aged Care Consumers (QOL‐ACC) [39] instrument. The HUI‐3 captures the sensory quality of life attributes and therefore will be more sensitive to the effect of the intervention. The interviewer‐administered version of the HUI‐3 was chosen as some participants will likely have mild cognitive impairment or dementia and therefore many may be unable to complete a self‐report measure. The QOL‐ACC will also be used to capture the quality of life as the HUI‐3 has shown inconsistencies in people with dementia. The QOL‐ACC has been validated both for people with dementia and people living in long‐term care [48] and is routinely collected by the Australian Government for long‐term care residents. We will measure QoL using both self‐assessed and proxy‐assessed versions of both HUI‐3 and QOL‐ACC to ensure completeness, where proxy‐assessment will be completed by the informal caregivers or long‐term care workers where an informal caregiver is not available. QOL‐ACC and HUI‐3 responses will be used to estimate utilities with an Australian algorithm [49, 50]. Utilities will be used to estimate quality‐adjusted life years (QALYs), which combine the utility of a health state with the time spent on that health state. QALYs will be used as the benefit measure in the cost‐effectiveness analyses. To capture the impact of the SSI on the duration of daily care delivery, a research assistant will use field notes to record the duration of daily care delivery based on direct observation of care workers entering and leaving the resident's room during baseline and post‐intervention periods.

Informal caregivers' quality of life will be evaluated using the 5‐item EQ‐5D‐5L [51], which evaluates five dimensions, including mobility, self‐care, usual activities, pain/discomfort and anxiety/depression. Higher scores reflect poorer quality of life. Utilities will be estimated using an Australian algorithm [51, 52].

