## Research Questions

2

This study uses prospective pre−post‐intervention trial design. The primary research question (RQ) is:

What is the impact of the SSI on the quality of life of residents and their informal caregivers (i.e., unpaid care provided by family, close relatives and friends) [37]? This RQ will be explored through standardised questionnaires (e.g., the Health Utilities Index 3 [HUI‐3] [38] and the Quality of Life‐Aged Care Consumers questionnaire [QOL‐ACC] [39], described below).

Secondary research questions include:

What is the impact of the SSI on care workers' (formal caregivers of people living in long‐term care) use of sensory support behaviours? This RQ will be explored through direct observation and questionnaires.

What is the impact of the SSI on residents' use of hearing and vision devices, quality of resident‐staff communication, well‐being, sensory function and behaviour? This RQ will be explored through direct observation, self (or proxy) report questionnaires and professional caregiver report.

What is the impact of the SSI on informal caregivers' well‐being and relationship with residents? This RQ will be explored through questionnaires.

What is the cost‐effectiveness of the SSI compared to standard care? This RQ will be explored through direct observation and questionnaires.

A simultaneous process evaluation is also planned to address the following research questions:

To what extent was the SSI considered acceptable to care workers, residents and informal caregivers and implemented as intended? Acceptability will be explored through a post‐intervention survey and individual structured qualitative interviews, and implementation will be evaluated based on inspection of daily task sheets that record the daily duties of care workers.

What were the mechanisms through which the SSI achieved/did not achieve impact? This RQ will be explored using individual, semi‐structured, in‐depth interviews.

How did contextual factors impact the implementation of the SSI? This RQ will be explored by analysing the written log completed by the sensory champion, supplemented by a structured qualitative interview.

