### Sample Size Calculation

3.3

Approximately 87 residents will be recruited at baseline. The evaluation is powered to detect a standardised effect size of *d* = 0.3 (because hearing/vision interventions are associated with small‐to‐medium effects on health‐related quality of life outcomes in the primary treatment group (i.e., residents) [40, 41, 42]. Assuming a correlation of 0.6 between baseline and 12‐week follow‐up Health Utility Index‐3 (HUI‐3) scores and an attrition rate of 20% at follow‐up (a conservative estimate based on the 12%–15% rates observed in previous similar studies) we will need to recruit 87 residents at baseline to achieve 80% power to detect the effect size at the two‐sided 5% level of significance, according to estimates generated by G*Power software [43].

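### The primary resident quality-of-life score may come from the resident, a caregiver or a trained care worker, with no rule holding the respondent constant, so any change of rater is confounded with time

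*Protocol article*

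**What the plan says.** Section 3.5.1 (Primary Outcome) names two instruments for residents, the HUI-3 and the QOL-ACC, and says of both: "We will measure QoL using both self‐assessed and proxy‐assessed versions of both HUI‐3 and QOL‐ACC to ensure completeness". It continues: "proxy‐assessment will be completed by the informal caregivers or long‐term care workers where an informal caregiver is not available". The same section expects that many residents may not manage a self-report measure because of cognitive impairment, and section 3.1 admits residents whatever their cognitive function. Section 3.5 describes the questionnaires as self- or proxy-report.

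Section 3.2 makes long-term care workers the direct target of the intervention: they are trained in device support, communication and noise reduction.

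On design, section 2 says: "This study uses prospective pre−post‐intervention trial design". There is no concurrent control. In section 3.6 the resident quality-of-life model has time as its independent variable. The potential covariates are demographics, health status, cognitive and sensory function, device use and care workers' support behaviours. Respondent type is not among them.

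**The concern.** The only contrast available for the primary question is change within residents over time. Such a contrast is clean only if the measurement is the same at each visit, and who gives the rating is part of the measurement.

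The stated proxy rule turns on availability: caregiver if there is one, care worker if not. Availability can differ between baseline, 3 months and 6 months, so the proxy's identity can change even within a series made up only of proxy ratings. If proxy scores are also used to fill gaps in self-report, a resident who answers at baseline but cannot answer later contributes a self-to-proxy difference to the time effect. Such switching would probably follow cognitive decline, so it would not be random, and no control arm is present to cancel it.

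A second strand does not depend on switching. Where the proxy is a care worker, the rater has received the intervention, is delivering it, and knows that the visit is after training. The rater's standard of judgement may move even when the rater stays the same.

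**Working it through.** **1. The plan's own figure.** Inputs from section 3.3: "The evaluation is powered to detect a standardised effect size of *d* = 0.3", "Assuming a correlation of 0.6 between baseline and 12‐week follow‐up", "an attrition rate of 20% at follow‐up", with 80% power at two-sided 5%.

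- Variance of the change, in baseline SD units: 2(1 − 0.6) = 0.8.
- Paired effect size: 0.3/√0.8 = 0.335.
- Completers, normal approximation: (1.960 + 0.842)²/0.335² = 69.8.
- Recruited: 69.8/0.8 = 87.2, which agrees with the stated 87.

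The exact noncentral-t calculation gives 72 completers, and 72/0.8 = 90. That difference is a separate matter and plays no part here. I use 70 completers (87 × 0.8 = 69.6), for which the standard error of the mean change is √(0.8/70) = 0.107 SD and exact power is 79%.

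**2. The bias formula.** Let f be the net share of completers whose rater changes after baseline, and g the new-minus-old rater difference in SD. If both ratings enter one change score, the expected change is the true effect plus f × g.

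**3. Ranges.** The article gives neither f nor g. Assumed: f from 10% to 30%, |g| from 0.2 to 0.5 SD. The sign of g is open.

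| f | \|g\| = 0.2 | \|g\| = 0.3 | \|g\| = 0.5 |
|---|---|---|---|
| 10% | 0.02 | 0.03 | 0.05 |
| 20% | 0.04 | 0.06 | 0.10 |
| 30% | 0.06 | 0.09 | 0.15 |

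Against the design effect: 0.02/0.3 = 7% and 0.15/0.3 = 50%.

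**4. What that does to the test.** Paired t-test, 70 completers, two-sided 5%. The variance of the change rises slightly with switching, to 0.8 + f(1 − f)g².

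| f, \|g\| | Two-sided rejection rate, no true effect | Power for true d = 0.3 if the new rater scores lower |
|---|---|---|
| none | 5% | 79% |
| 10%, 0.2 | 5% | 73% |
| 20%, 0.5 | 15% | 44% |
| 30%, 0.5 | 27% | 27% |

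If the new rater scores higher, the estimate is inflated by the same amounts. With no true effect, nearly all the excess rejections at the larger biases then fall on the side of benefit.

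**5. The boundary case.** If every resident's change is computed within one respondent, f = 0 and this bias is zero, whatever g is. What is left is any shift in a care worker's own rating standard after training. This formula does not cover it and the documents do not allow it to be sized.

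**The case against.** The strongest reply is that the sentence describes parallel collection: both versions of both instruments, for everyone. Elsewhere, in section 3.5.2, the authors mark self and proxy as alternatives by putting the proxy version in brackets. On the parallel reading, a resident who loses capacity already has a proxy series, and no self-to-proxy difference need enter any change score. A reader might infer from the completeness wording that the plan mixes raters and will count a change of rater as an intervention effect. The documents do not support that: no passage says that the scores are pooled or that raters change between visits.

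Further points in the plan's favour:

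- Which score is primary and how the two are combined may be set out in the full protocol or analysis plan, neither of which is shown. Their absence from an article is not a fault in itself.
- Care workers are a fallback only. The Abstract plans 87 residents and 87 informal caregivers, roughly one each, so care-worker proxies should be a minority.
- Residents and caregivers also know when a visit follows the intervention.
- A reader might infer that analysing two versions inflates the error rate unchecked. Section 3.6 already plans family-wise error control for each research question.
- Interviewer administration, and an instrument described as validated in dementia, should help to preserve self-report.

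All of this stands, and it makes the point conditional. It does not dispose of the stated proxy rule. That rule lets the proxy's identity follow availability, even within a parallel proxy series, and it makes recipients of the intervention raters of the primary outcome.

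**Conclusion.** The point holds in conditional form and merits a change. The article names three kinds of respondent for the primary outcome, one of them the group being trained, and gives no rule that keeps the respondent the same across visits. The effect is a time term without a control arm. If self and proxy scores are combined, or if the proxy moves between caregiver and care worker, the rater shift cannot be separated from the intervention effect.

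The size is illustrative: 0.02 to 0.15 SD against a design effect of 0.3. It rests wholly on the assumed 10% to 30% net switching and 0.2 to 0.5 SD rater difference, and it may inflate or mask an effect. A reader might infer that care-worker ratings will tilt towards improvement. That is a risk, and nothing in the documents establishes its direction. With a constant respondent the switching bias is nil.

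**What to change.** State in section 3.5.1 and carry into section 3.6:

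1. At baseline, record one respondent source for each resident: self if able, otherwise a named proxy. Compute primary change only within one source.
2. Collect the proxy version from the same named proxy at every visit, from baseline onwards. A resident who loses capacity then has a proxy-to-proxy change. A baseline proxy rating that was not taken cannot be recovered later.
3. Include respondent type (self, informal caregiver, care worker) in the model.
4. Report a sensitivity analysis without care-worker-proxied scores, but keep those residents in the primary analysis. Excluding them outright could remove a non-random group, namely residents who cannot self-report and have no informal caregiver, and would reduce a sample already discounted for 20% attrition.

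The cost is mostly wording, plus consistent use of forms already planned and a record of who completed each one. Some residents will contribute proxy-only change. A few may have no same-source follow-up if a named proxy leaves, and these should be counted and reported as missing and not filled from another rater.

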#### Secondary Outcomes

3.5.2

To evaluate the impact of the SSI on long‐term care workers' use of sensory support behaviours (RQ2), care workers' hearing aid and glasses management knowledge and skills will be assessed, sound and light measurements will be taken and task lists that record the daily duties of care staff will be reviewed. Hearing aid and glasses management knowledge and skills will be assessed at three time points (baseline, after the training intervention and after 3 months follow‐up) using modified versions of the Hearing Aid Skills Knowledge assessment and the Glasses Skills Knowledge assessment [53, 54]. Background noise and lighting levels will be recorded using observational measures including a modified version of the Mealtime Scan [55] as well as sound and light measurements in residents' rooms, corridors and communal dining areas. The Mealtime Scan is a tool to quantify the overall dining environment by assessing the physical and social environments as well as person‐centred care practices [55]. For the current study, the Mealtime Scan was adapted to focus on social interactions and sound measurement during the meal. Four observations will be made at baseline, 3 months and 6 months. Sound and light levels will be measured using a Protech Pro Sound Level Metre and a Protech Professional 400 K Lux Metre. In common areas, the average of three measurements will be recorded at each of the four central points of a square grid covering the extent of the room: the top‐left, top‐right, bottom‐left and bottom‐right. In residents' rooms, two light measurements will be taken: one measurement of ambient light levels and another from a location where the resident typically performs activities (e.g., reading in bed, armchair or table). Long‐term care workers' task lists will be reviewed to verify completion of sensory support tasks, including device management, use of communication strategies and background noise reduction over a period of 3 days at baseline and post‐intervention.

To evaluate the impact of the intervention on residents' use of hearing and vision devices, quality of resident‐provider communication, well‐being, sensory function and behaviour (RQ3), we will employ direct observation, self (or proxy) report questionnaires and professional caregiver report. The use of hearing and vision devices will be measured using direct observation and resident self‐report. Residents will complete the International Outcome Inventory‐Hearing Aids (IOI‐HA) if they own hearing aids [56]. Items on the IOI‐HA are scored on a 5‐point Likert scale from left (worst) to right (best), with higher scores representing better hearing aid outcomes. Resident‐provider communication will be measured using two subscales of the Patient Evaluation of Emotional Care During Hospitalisation (PEECH) questionnaire [57, 58] capturing ‘level of personal value’ (10 items) and ‘level of connection’ (3 items). Items are measured on a 4‐point scale (3 = all, 2 = most, 1 = some, 0 = none) with higher scores reflecting better patient‐provider communication. Overall well‐being will be measured using the 20‐item Geriatric Anxiety Inventory [59] and 8‐item Geriatric Depression Scale (nursing home version) [60]. Participants are asked to respond with yes/no to a series of statements that ask about symptoms of anxiety and depression. Functional and social impacts of hearing loss will be evaluated using the 5‐item Social Isolation Measure using an 11‐point Likert scale [61] and the 10‐item Revised Hearing Handicap Inventory—Screening (or proxy version) where each item is assigned a score of 4, 2 or 0 [62]. Both measures ask about the social and emotional impacts of hearing loss, with higher scores being indicative of more perceived hearing‐related activity limitations and participation restrictions. Vision function will be measured using the 20‐item Veterans Affairs Low Vision Visual Functioning Questionnaire–short form (LV‐VFQ‐20) (or proxy version) [63], which asks about the impact of corrected vision in four domains: reading, visual motor, visual information processing and mobility. Each item is measured on a 5‐item scale: ‘not difficult’, ‘slightly/moderately difficult’, ‘extremely difficult’, ‘impossible’ and ‘do not do it for nonvisual reasons’. The presence of responsive behaviours will be evaluated by professional care staff using the Neuropsychiatric Inventory–care home version (NPI‐NH) [64]. Lastly, routinely collected data pertaining to the National Aged Care Quality indicators (e.g., medication management, falls and major injury) will be extracted from participants' long‐term care records.

To evaluate the impact of the SSI on informal caregivers' well‐being and relationships with the residents (RQ4), overall well‐being will be measured using the 12‐item General Health Questionnaire (GHQ‐12) [65], and relationship satisfaction will be measured using the 7‐item Burns Relationship Satisfaction Scale [66]. Higher scores reflect higher levels of mental distress and greater relationship satisfaction, respectively.

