### SSI

3.2

The SSI is twofold. First, we will be intervening directly with long‐term care workers to support them to carry out three target behaviours: (1) assist residents with day‐to‐day hearing and vision device use, (2) use appropriate communication and (3) mute TV/radio at the bedside and during mealtimes when communicating. These behaviours are fully specified in Table 1. We will be carrying out a multifaceted intervention that addresses the key barriers and enablers identified in our exploratory Phase 1 research [32, 33, 34], as described in Table 2. Second, one or two staff at each participating site will be assigned a ‘sensory champion role’. Previous studies have shown that designating one or more staff members as ‘champions’ in long‐term care facilities and providing them with additional training and responsibilities can enhance their competence in managing related issues, improve the quality of care and positively impact the health outcomes of residents [35]. A subsequent study reported that designated ‘hearing champions’ were effective in supporting staff in relation to the maintenance of hearing aids and the use of communication strategies for residents with hearing impairment [36]. The sensory champion may be a registered nurse, care worker or therapy assistant, and will be employed in this capacity for 2−3 days per week for 3 months at each site. A description of the tasks completed by the sensory champion is outlined in Table 3.

**Table 1 hex70175-tbl-0001:** Full specification of staff behaviours targeted in the sensory support intervention.

Behaviour	Full specification
Assist residents with day‐to‐day hearing/vision device use	Each morning, check glasses are on and clean (glasses wearers) Each morning, check that hearing aids are on, inserted correctly and on correct ears and working (HA users) Each evening, check hearing aids and personal listening devices are removed, wiped clean and stored safely and batteries are conserved (on charge/battery door open) (HA/ALD users) Each week, check frames are well aligned and in good order (e.g., screws tight, nose pads intact, no corrosion of metal frames or fragmentation of plastic) (glasses wearers)
Use appropriate communication	Gain attention Speak face‐to‐face Speak clearer, nearer, slower Make text brighter, bigger, bolder

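### No RQ2 measure is specified as observing the Table 1 communication acts, and the only RQ2 source that names communication is a task list that the intervention itself rewrites

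*Protocol article*

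**What the plan says.** The Research Questions section of the protocol article sets RQ2 as the effect of the SSI on care workers' "use of sensory support behaviours? This RQ will be explored through direct observation and questionnaires".

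Section 3.2 lists three target behaviours, of which appropriate communication is the second. Table 1 specifies it as acts that an onlooker could see or hear: "Gain attention Speak face‐to‐face Speak clearer, nearer, slower Make text brighter, bigger, bolder".

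Section 3.5.2 gives the RQ2 sources. Staff are tested on hearing aids and glasses; in addition, "sound and light measurements will be taken and task lists that record the daily duties of care staff will be reviewed". The observational part opens with this purpose: "Background noise and lighting levels will be recorded using observational measures including a modified version of the Mealtime Scan". The same paragraph then says that the Scan was reworked to concentrate on social interaction and sound at meals, with four observations at baseline, 3 months and 6 months. Communication is named only in the last source, where staff "task lists will be reviewed to verify completion of sensory support tasks, including device management, use of communication strategies and background noise reduction", over 3 days at baseline and post-intervention.

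Table 2 describes the sensory support goal-setting component of the SSI. It builds items on device use, effective communication and noise reduction into the daily task list.

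**The concern.** A task list can record that communication support was done on a given day. It cannot show whether the worker gained attention, faced the resident or slowed down across the day's exchanges. For this behaviour, the source that the plan names is neither an observation nor a questionnaire, although RQ2 is said to rest on those two.

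The list is also part of the treatment. If the SSI puts a communication item on it, a before-and-after comparison of completion partly measures the arrival of the item. The Research Questions section further assigns daily task sheets to the process evaluation, as evidence of whether the SSI was implemented as intended. The same kind of record then serves as intervention component, fidelity measure and RQ2 outcome.

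At stake is the RQ2 answer for one of the three behaviours that the SSI is built to change. It could be reported as behaviour change when only record-keeping had changed. Section 3.6 also lists workers' sensory support behaviours as a potential covariate in the resident and caregiver models. If task-list completion supplies that covariate, which the article does not say, the same weakness goes with it.

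**Working it through.** No figure in the plan depends on this point: the sample size of 87 is for residents' HUI-3. The check is to set each RQ2 source in section 3.5.2 against the three target behaviours in section 3.2.

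| RQ2 source | Device assistance | Communication | Noise reduction |
|---|---|---|---|
| Hearing aid and glasses assessments | knowledge and skills | not covered | not covered |
| Sound and light readings | not covered | not covered | measured (sound) |
| Modified Mealtime Scan | not stated | social interaction at meals; no stated link to Table 1 | sound at meals |
| Task-list review | named | named | named |

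The communication column has one source that names the behaviour, and it is a completion record. It has one observed source that may bear on it, but its stated purpose is noise and lighting and its reach is the meal.

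Two measures outside RQ2 were also checked.

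- **PEECH (RQ3, section 3.5.2).** Two subscales, 10 items on personal value and 3 on connection. This is the resident's view of the relationship; it does not score the Table 1 acts.
- **Observation of care delivery (section 3.5.1).** A research assistant times workers entering and leaving the room. The stated purpose is duration.

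Next, what the task-list comparison can show. Let the recorded rate be the share of reviewed lists on which a communication item is present and marked complete.

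- If there is no such item at baseline, the baseline rate is 0 whatever staff do. With a post-intervention rate of c, the change is c − 0 = c. Any c above 0 appears as a gain, even if staff communicate exactly as before.
- If an equivalent item was already there, the change is c1 − c0. This removes the artefact of a new item but is still a change in marking, not in observed communication.

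The article does not describe the baseline list. Table 2 presents the integration of these items as something the SSI does, which makes the first case the more natural reading. The objection to using completion as the behavioural outcome holds in both cases.

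**The case against.** The best counter-argument is the Mealtime Scan. It sits in the RQ2 paragraph, it is an observation, it is repeated at all three time points, and its adaptation concentrates on social interaction. In its general form it also covers person-centred care practices. Its items are not shown, and a journal article commonly leaves item lists to the full protocol, so it may already code some of the Table 1 acts. This stands in part. A reader might infer that RQ2 has no observation of communication at all, or that it cannot show any change; the article does not support either reading. The absence of an item list is not the complaint. The complaint is the stated choice to verify communication strategies by completion of a list that the SSI alters.

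A second argument is that communication is measured under RQ3 by PEECH and modelled over time, and that device use, too, is observed under RQ3 and not RQ2. This also stands in part: the trial will have the residents' view. But PEECH addresses whether residents feel valued and connected. It cannot say which staff acts changed.

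A reader might also infer that the mechanism question (RQ7) fails for the same reason. It does not: section 3.5.3 explores mechanisms through in-depth interviews with about 20 care workers, not through task lists.

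**Conclusion.** The point holds in a limited form. No RQ2 measure is specified as observing the Table 1 communication acts; the one source that names communication is completion of a list that the SSI changes, and its before-and-after difference can be an artefact.

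The size is one of three target behaviours, in a secondary question. The primary outcome measures are not touched. RQ2 as written gives weak and indirect evidence on communication, through the Scan's social-interaction content. No numerical bias can be given, because the article states neither the baseline list content nor any expected completion rates.

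The conclusion rests on two readings: that Table 2 means communication items are added by the SSI, and that the Scan's role is the one section 3.5.2 states. If the full protocol already ties Scan items to the Table 1 acts, the remaining step is to name those items as the outcome and to move the task-list entry out of that role.

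**What to change.** In section 3.5.2, make the Mealtime Scan's social-interaction observations the RQ2 outcome for target behaviour 2. Name the existing items, or add a few, that score for each staff-resident exchange seen: attention gained, face to face, and clearer/nearer/slower speech. Report the proportion of exchanges that meet them at baseline, 3 and 6 months. Keep the task-list communication entry as a fidelity record, not an outcome. If this is not done, state that RQ2 does not directly test communication.

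Section 3.6 allows a repeated measures test other than the paired *t*-test. That latitude is needed here, because exchanges are grouped within meals and will not pair by worker unless the worker is recorded.

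The cost is a few items and a coding guide in a tool that is already being modified, at observations already planned, with no new staff or sessions. There are downsides: some added coding load while sound is also being measured, an observer who knows the study phase, sampling of mealtimes only, and few observed meals, so estimates will be imprecise. The text-format act in Table 1 stays unobserved. RQ2 conclusions on communication should be limited to match.
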